### Design and study population

2.1

We will perform a prospective observational cohort study in the Echocardiography and Non‐invasive Cardiology Laboratory of the Hospital Universitario de Canarias. The study population will comprise patients referred for TTE (Figure 1).

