### Sample size calculation

2.7

Previous data suggested that 92% of patients with LA abnormality might have a positive Morris index (Morris et al., 1964). We estimate that 79 patients with a positive Morris index are required to determine this rate with a confidence level of 95% and precision error of 6%.

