### Statistical analysis

2.8

Continuous variables will be compared using the *t* test or the Mann–Whitney test. Categorical variables will be compared using the chi‐square test. Based on the volume of LAV max by echocardiography, 2 groups will be established, as follows: increased volume and normal volume. Correlations between ECG and TTE STE variables will be obtained using the Spearman rank test and the intraclass correlation coefficient. We will use the logistic regression model adjusted for potential confounders, including variables that are significant in the univariate model. The ability of the multivariate logistic model to correlate with the LAV max group will be verified using receiver operating characteristic (ROC) curves. The overall accuracy, sensitivity, specificity, and positive and negative predictive values for the optimal cutoff will be calculated using the Youden index. Intra‐ and interobserver variability will be assessed using Bland–Altman analysis. All statistical analyses will be performed using IBM SPSS Statistics for Windows, Version 23 (IBM Corp., Armonk, NY, USA).

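### Section 2.8 reports the multivariable model's accuracy at a searched Youden cutoff in the same patients that chose and fitted the model, so those figures will on average be too favourable

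*Protocol article*

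**What the plan says.** The data come from one prospective cohort in one echocardiography laboratory (Section 2.1): "The study population will comprise patients referred for TTE". Section 2.8 then sets out a sequence.

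- **Outcome.** Patients are split on maximal left atrial volume: "2 groups will be established, as follows: increased volume and normal volume". Section 2.5 puts the limit at 34 ml/m².
- **Selection and fitting.** "We will use the logistic regression model adjusted for potential confounders, including variables that are significant in the univariate model".
- **Assessment.** The model's ability to correlate with the volume group "will be verified using receiver operating characteristic (ROC) curves".
- **Reported accuracy.** Overall accuracy, sensitivity, specificity, "positive and negative predictive values for the optimal cutoff will be calculated using the Youden index".

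The article names no hold-out sample, cross-validation, bootstrap or external cohort. Section 2.7 sizes the study for one proportion, not for a model: "We estimate that 79 patients with a positive Morris index are required". It gives no total sample size.

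**The concern.** Four operations draw on the same patients: choosing the variables, estimating the coefficients, finding the cutoff, and measuring accuracy at that cutoff. Each of the first three adapts to chance features of the sample, and the fourth counts that adaptation as performance. An ROC curve on the fitting data describes how well the model separates these patients. It does not show how the model and cutoff would do in the next ones.

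The Introduction presents low sensitivity as the weakness of existing ECG criteria, and the Conclusion expects the study to help define criteria. An inflated sensitivity at a searched cutoff bears directly on that question. It could make a weak model look better than the fixed criteria it is set beside.

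**Working it through.** **1. The plan's own figure.** Section 2.7 uses p = 0.92, half-width d = 0.06 and 95% confidence. n = 1.96² × p(1 − p)/d² = 3.8415 × 0.0736/0.0036 = 78.5, rounded up to 79. The figure reproduces, and the sample size arithmetic is not in question here.

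**2. Direction.** For a score with cutoff c, J(c) = Se(c) + Sp(c) − 1. The Youden cutoff ĉ maximises the sample estimate Ĵ. Even for a score fixed in advance, E[Ĵ(ĉ)] ≥ max J(c) ≥ E[J(ĉ)]. The reported value is therefore too high on average, and the chosen cutoff does no better in new patients than the best cutoff. Screening and coefficient fitting add to this.

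**3. Size: inputs.** The article does not give total N, the candidate list, the prevalence of increased volume or the effect sizes, so all four are assumptions. For the number of candidates, Table 2 has 21 demographic and clinical items. Section 2.4 lists about 9 left atrial parameters (area and axis counted separately) and 4 right atrial ones. That gives 13 ECG items, or 21 + 13 = 34 in all, before the 12 echocardiography indications.

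**4. Simulation.** Candidates are independent normal variables. The steps are t-test screening at p < 0.05, logistic fit and Youden cutoff. The same model and cutoff are then applied to 20,000 new patients. There are 600 runs per row, averaged over runs that selected at least one variable (578 of 600 in the first row, 476 of 600 in the last). Real predictors: three, log odds ratio 0.5 per SD. Entries are same patients / new patients, with the excess in points.

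| N | Candidates | Prevalence | Sensitivity | Specificity | AUC |
|---|---|---|---|---|---|
| 79 | 30 | 50% | 0.723 / 0.563 (16.0) | 0.735 / 0.597 (13.8) | 0.760 / 0.619 |
| 79 | 10 | 50% | 0.705 / 0.581 (12.4) | 0.708 / 0.600 (10.8) | 0.727 / 0.637 |
| 158 | 30 | 50% | 0.699 / 0.607 (9.2) | 0.702 / 0.615 (8.7) | 0.739 / 0.662 |
| 200 | 30 | 50% | 0.692 / 0.616 (7.6) | 0.699 / 0.624 (7.5) | 0.736 / 0.674 |
| 400 | 30 | 50% | 0.686 / 0.642 (4.4) | 0.679 / 0.637 (4.2) | 0.730 / 0.697 |
| 400 | 10 | 50% | 0.675 / 0.641 (3.4) | 0.675 / 0.647 (2.8) | 0.720 / 0.706 |
| 79 | 30 | 30% | 0.754 / 0.500 (25.4) | 0.735 / 0.635 (10.0) | 0.775 / 0.603 |
| 79 | 30, none real | 50% | 0.684 / 0.491 (19.3) | 0.686 / 0.509 (17.7) | 0.698 / 0.500 |

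**5. Other settings.**
- N = 198, prevalence 40%, 34 candidates, two real at log odds ratio 0.4: AUC 0.69 against 0.60 and J 0.33 against 0.14. That is 19 to 20 points on the sum, or about 10 each on average.
- As above with 8 candidates: AUC 0.67 against 0.63, J 0.30 against 0.18.
- N = 400, 13 candidates, four real at 0.5: sensitivity 0.70 against 0.66, specificity 0.69 against 0.67.
- Cutoff search alone on one marker, with no model: 0.734 − 0.677 = 5.7 points of sensitivity and 0.693 − 0.648 = 4.5 of specificity at N = 79; 2.1 and 1.8 points at N = 400.

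**6. Predictive values.** These inherit the bias. With the first row's averages at 50% prevalence, PPV = Se/(Se + 1 − Sp). In the same patients this is 0.723/(0.723 + 0.265) = 0.73; in new patients it is 0.563/(0.563 + 0.403) = 0.58.

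**The case against.** The strongest reply is that this is a condensed article. A fuller plan, not shown, could contain internal validation, and its absence here would then be no fault. That holds for the detail of resampling. It does not dispose of the point, because the article does state its verification step, an ROC curve of the fitted model, and states that accuracy is taken at the searched optimum. Followed as written, that yields optimistic figures.

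Second, the model is described in terms of adjustment and correlation with the volume group, not validated prediction. A reader might infer that the ROC step is worthless. That goes too far: an apparent AUC is a legitimate description of discrimination in the sample. The fault lies in treating it as verification and in reporting searched accuracy uncorrected.

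Third, a reader might extend the bias to all the study's diagnostic results. The documents do not support that. Most left atrial criteria in Section 2.4 have thresholds fixed in advance (120 and 140 ms, 0.10 and 0.20 mV, axis −30 to −45º), and the Introduction gives the Morris thresholds. Their accuracy involves no search. The Morris proportion in Section 2.7 is untouched.

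Fourth, the larger excesses come from small samples, many candidates and weak signals. Candidates such as height, weight, BMI and BSA, or the two stroke-risk scores, overlap, although adding correlation in the N = 198 setting changed little (J 0.32 against 0.16). A larger cohort or a short candidate list shrinks the excess considerably. This objection stands, and it is why the size must be given as a range.

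**Conclusion.** The point holds for the multivariable model and its Youden cutoff. The upward direction is certain in expectation and appeared in every setting tried. With real predictors, the excess runs from about 2 to 4 points each of sensitivity and specificity (N = 400, few candidates, stronger signal) to about 7 to 16 points each (N = 79 to 198, 30 or more candidates, weaker signal, prevalence 40 to 50%). At 30% prevalence and N = 79 the split is uneven, about 25 points of sensitivity and 10 of specificity. With no real predictor at N = 79 and 30 candidates it is 18 to 19 points each. All of these rest on assumed N, candidates, prevalence and effects.

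Three further inferences are tempting but unsupported. The loss of about 20 points at N = 198 is a sum of two measures in one unfavourable setting, not an estimate for this study. Section 2.8 mentions no confidence interval for these accuracy measures, so no interval method can be faulted. The 79 in Section 2.7 is stated as Morris-positive patients, so it cannot be taken as the number with left atrial abnormality or as the total; the N = 79 rows are only the small end of a range.

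This should be corrected before analysis. It does not undermine the main association aim.

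**What to change.** In Section 2.8:

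- Report optimism-corrected AUC, sensitivity, specificity and predictive values by bootstrap with at least 500 resamples. In each resample, repeat univariate selection, logistic fitting and the Youden search. Apply the resulting model and cutoff both to the resample and to the original cohort. The corrected value is the apparent value minus the mean of (resample performance − original-cohort performance).
- Fix the candidate list beforehand, so that selection can be repeated, and state what happens when no variable is selected.
- Describe the ROC curve as apparent discrimination, and label the model's Youden cutoff exploratory.
- Report the accuracy of the fixed-threshold ECG criteria separately; they need no such correction. They answer a different question and cannot replace a cutoff on the model's score.

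The cost is analysis code, probably outside the standard menus of the SPSS version named, and less favourable reported accuracy. No new patients or measurements are needed.

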### Ethical considerations

2.9

This study will be reviewed and approved by the Clinical Research Ethics Committee of Hospital Universitario de Canarias. All participants will be informed about the aims and procedures of the project and will sign a written informed consent document. The project will be conducted in accordance with the World Medical Association Declaration of Helsinki related to Ethical Principles for Medical Research Involving Human Subjects, the Convention on Human Rights and Biomedicine of the Council of Europe (1997), and the Additional Protocol to the Convention on Human Rights and Biomedicine, concerning Biomedical Research (2005).

### Study timeline

2.10

The study is expected to begin in June 2020. The estimated end of the inclusion period is July 2020, and the estimated completion date for the study is September 2020.

## CONCLUSION

3

Our prospective observational study will help to define ECG criteria for LA and RA abnormality and to distinguish IAB from LA abnormality.
